### Outcome measures

The primary outcome measure will be change from baseline to week 12 in the patient-reported outcome Disabilities of the Arm, Shoulder and Hand (DASH) questionnaire (0 to 100 score, 100 = no problems) [36], and reported as the difference in mean change between the groups. The secondary endpoint assessment on the primary outcome will be performed 12 months after baseline (Figure 1).

The secondary outcome, measured at baseline and after 12 weeks, will include: the Shoulder injury and Osteoarthritis Outcome Score (SOOS; 0 to 100 score, 100 = no problems) [37], the Hospital Anxiety and Depression Scale (HAD Scale; 0 to 21 score, 0 = no problems) [38], EuroQol instrument (EQ-5D index; −0.59 to 1 score, −0.59 = lowest health-related quality of life), EuroQol Visual Analogue Scale (EQ-VAS; 0 to 100 score, 0 = lowest health-related quality of life) [39], perceived pain at rest, general activity and maximum pain experienced during the previous 24 hours (visual analogue scale, 0 to 100 score, 0 = no pain) [40], maximum isometric voluntary contraction (MVC) of external and/or internal rotation and scaption measured by dynamometers, active and passive range of movement in scaption (0 to 180 degrees), external (0 to 90 degrees) and internal rotation (0 to 90 degrees) measured by goniometer, clinical tests (Scapula Assistance Test [41], Scapula Retraction Test (positive or negative) [42] and ultrasonography measurements (aggregated sum of: supraspinatus tendon thickening (grade 0 to 3), fibrillar disruption (grade 0 to 3), calcification (grade 0 to 3) and neovascularisation (grade 0 to 4) [33]).

The following secondary outcomes will only be measured at the 12-month follow-up assessment: number of patients referred for, or completed, arthroscopic subacromial decompression; patients given subacromial corticosteroid injections after the intervention period; the number of visits to a general practitioner or secondary healthcare setting due to the shoulder problem (registration in the Danish Central Office of Patient Registration); and economic variables (for example, patient-reported number of sick days from work and sport attributed to the shoulder and time spent on rehabilitation in the trial period and post-trial, (patient-reported and register-controlled). Table 1 presents all outcome measures and at which time point they will be collected.

**Table 1 Tab1:** **Summary of measures to be collected**

**Article number**	**Variable**	**Baseline**	**Week 3**	**Week 6**	**Week 9**	**Week 12**	**Week 52**
Socio-demographic measurements							
1, 2, 3	Age - year	Yes	n/a	n/a	n/a	n/a	n/a
1, 2, 3	Female sex – number (%)	Yes	n/a	n/a	n/a	n/a	n/a
1, 2, 3	Duration of symptoms - year	Yes	n/a	n/a	n/a	n/a	n/a
	Symptom history						
1, 2, 3	- Accident or acute incidence	Yes	n/a	n/a	n/a	n/a	n/a
1, 2, 3	- Slow consistent development (overload)	Yes	n/a	n/a	n/a	n/a	n/a
1, 2, 3	- Fluctuating development	Yes	n/a	n/a	n/a	n/a	n/a
	Compliance with exercise protocol						
1, 2, 3	- Visits to the physiotherapy department	n/a	n/a	n/a	n/a	Yes	n/a
1, 2, 3	- Exercise diary	n/a	n/a	n/a	n/a	Yes	n/a
1, 2, 3	- Pain diary	n/a	n/a	n/a	n/a	Yes	n/a
Patient reported and physiological measurements							
1, 2, 3	Disabilities of the Arm, Shoulder and Hand (DASH) questionnaire (range: 0 to 100) [36]	Yes	Yes	Yes	Yes	Yes	Yes
1,2	Shoulder injury and Osteoarthritis Outcome Score (SOOS) [37]	Yes	n/a	n/a	n/a	Yes	Yes
1, 2	Hospital Anxiety and Depression Scale (HAD Scale, range: 0 to 21) [38]	Yes	n/a	n/a	n/a	n/a	n/a
1, 2	Visual analogue pain scale (VAS, range: 0 to 100) [40]						
	- Rest	Yes	n/a	n/a	n/a	Yes	n/a
	- Maximum	Yes	n/a	n/a	n/a	Yes	n/a
	- Activity	Yes	n/a	n/a	n/a	Yes	n/a
	Isometric strength						
1, 3	- Scaption	Yes	n/a	n/a	n/a	Yes	n/a
1, 3	- External rotation	Yes	n/a	n/a	n/a	Yes	n/a
1, 3	- Internal rotation	Yes	n/a	n/a	n/a	Yes	n/a
	Degree of active movement						
1, 3	- Scaption	Yes	n/a	n/a	n/a	Yes	n/a
1, 3	- External rotation	Yes	n/a	n/a	n/a	Yes	n/a
1, 3	- Internal rotation	Yes	n/a	n/a	n/a	Yes	n/a
	Positive clinical test – number (%)						
3	- SAT [41]	Yes	n/a	n/a	n/a	Yes	n/a
3	- SRT [42]	Yes	n/a	n/a	n/a	Yes	n/a
	Ultrasonographic measurement [33]						
1	- Hypoechoic scale (range: 0 to 3)	Yes	n/a	n/a	n/a	Yes	n/a
1	- Neovascularity scale (range: 0 to 4)	Yes	n/a	n/a	n/a	Yes	n/a
1	- Tendon swelling – mm	Yes	n/a	n/a	n/a	Yes	n/a
1	- Calcification (range: 0 to 3)	Yes	n/a	n/a	n/a	Yes	n/a
Socio-economic measurements							
	Referred to						
1, 2	- Operation – number (%)	n/a	n/a	n/a	n/a	Yes	Yes
1, 2	- Corticosteroid injection(s) – number	Yes	n/a	n/a	n/a	Yes	Yes
	Shoulder related						
2	- Visits to general practitioner – number	n/a	n/a	n/a	n/a	Yes	Yes
2	- Visits to secondary healthcare setting – number	n/a	n/a	n/a	n/a	Yes	Yes
2	- Sick days – number	n/a	n/a	n/a	n/a	Yes	Yes
2	Time spent on shoulder-related rehabilitation - hours	n/a	n/a	n/a	n/a	Yes	Yes
2	EuroQol-5D (EQ-5D, range: 0 to 100) [39]	Yes	n/a	n/a	n/a	Yes	Yes

n/a: not assessed; SAT: Scapulae Assistance Test; SRT: Scapulae Retraction Test.

Article 1: Progressive high-load exercise compared with general low-load exercise in patients with rotator cuff tendinopathy: a randomised trial.

Article 2: The effect of 12 weeks of progressive high-load exercise in patients with rotator cuff tendinopathy on patient-reported and economic outcomes – 12 months follow-up.

Article 3: The prognostic evaluation of clinical tests in patients with rotator cuff tendinopathy.

Demographic data and other measurements will be recorded, covering socio-economic variables such as: employment, education, statement of income, history of injury (for example, accident, slow development and fluctuations), duration of current symptoms and physical demands in work and/or hobby activities (patient-reported).

The patients will be instructed to complete an exercise and pain diary. In the exercise diary, the patients will be asked to report the number of sets and repetitions per set for every training session, as well as the load during the exercise. Self-reported pain will be registered immediately before and 30 minutes after each training session. All pain measurements will be reported on the Numeric Pain Rating Scale. In addition to pain, patients will be asked to report use of analgesics (type and amount).

Good compliance will be defined by attendance at four out of the six visits to the physiotherapist, and an 80% complete exercise diary, where 100% will be defined by performance of 36 sessions of training (12 weeks at three training sessions per week).

### Data collection

Three outcome assessors will perform all enrolment, baseline and follow-up assessments. Before starting the data collection, the assessors will train together with the primary investigator and decide on a consensus standard of interpreting all outcome variables.

### Sample size and power considerations

Studies on patients with SIS have shown mean baseline values for DASH scores between 18 and 65, and standard deviations (SD) between 12 and 20 [30,31,43-47]. Often a 50% reduction in DASH score is seen after treatment [30,31,44,46,47], and it is suggested that a 40% change corresponds to a substantial improvement for the patient [46]. Based on these data, we expect a mean baseline of 40 points on the DASH questionnaire with an SD of 17. We expect a 50% change (change from 40 to 20 DASH points) in the progressive high-load exercise group, and 25% (change from 40 to 30 DASH points) in the low-load exercise group (Figure 2A).

**Figure 2 Fig2:**
[figure not shown]
**Anticipated outcome (primary and secondary objectives). A**: (Primary objective) Illustration of expected DASH score at 12 weeks. Black = intervention group, White = control group. **B**: (Secondary objective) Illustration of expected DASH score at 12 weeks stratified for concomitant corticosteroid injection. Columns I + II = intervention group, Columns III + IV = control group, Black = concomitant corticosteroid injection, White = no concomitant corticosteroid injection. DASH, Disabilities of the Arm, Shoulder and Hand Questionnaire.

For a two-sample pooled t-test of a normal mean difference with a two-sided significance level of 0.05 (*P* ≤0.05), assuming a common SD of 17 DASH points, a sample size of 100 patients per group has a power of 0.985 (>95% power for the primary outcome) to detect a between-group mean difference of 20 and 30 DASH points after 12 weeks in the progressive high-load exercise group and the low-load exercise group, respectively.

As the second objective is to explore the interaction between corticosteroid use (yes or no) and exercise (progressive high-load exercise or low-load exercise), it is hypothesised that, in the high-load group receiving corticosteroids at baseline, the DASH score at endpoint (12 weeks) will be more favourable than those without corticosteroids. With an SD of 17 DASH points, a sample size of 62 patients per stratum (having progressive high-load exercise) will be required to obtain a power of at least 0.9 (90%) to detect a mean difference of 10 DASH points between the two subgroups within the progressive high-load exercise group (Figure 2B). Consequently, it is decided to include 260 patients in the study, assuming a similar number of patients injected and not injected with corticosteroids (1:1; 2 × 130 patients randomly assigned to each exercise group (progressive high-load exercise versus low-load exercise)).

A final deadline for patient recruitment is set at Marts 2015, meaning that patient recruitment stops when the total number of 260 patients has been recruited, or the deadline of Marts 2015 is reached. In case the target number of 260 patients has not been met within the specified recruitment period, the power of the study will be less than expected. With an SD of 17 DASH points, a sample size of 46 patients per group will be required to obtain a power of at least 0.8 (80%) to detect a mean difference of 10 DASH points between the two groups.

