The aim of the study is to determine in a randomised, double-blind controlled trial if a progressive high-load exercise programme for the rotator cuff muscles is superior to a traditional low-load exercise programme in patients with rotator cuff tendinopathy, based on the primary endpoint; change in score on the Disabilities of the Arm, Shoulder and Hand (DASH) questionnaire [36] after 12 weeks of exercise. The second aim is to evaluate the possible interaction of concomitant use of corticosteroids with the exercise intervention.

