Concomitant use of corticosteroid injections will be based on the orthopaedic specialist’s evaluation, in accordance with the department’s standard procedures. Between 25 and 50% of patients are expected to receive injections. The corticosteroid injections will be given to patients at the shoulder unit of the orthopaedic departments, after baseline assessment but before randomisation. Randomisation will be performed in a stratified manner to ensure even distribution of patients receiving and not receiving corticosteroid injections in the two exercise groups.

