### Statistical analysis plan

The primary efficacy analysis performed is assessment of the between-group difference in change in the DASH score after 12 weeks in the intent-to-treat (ITT) population (all randomised patients independent of compliance and withdrawals). In the case of missing data due to drop-outs, a non-responder imputation will be applied; a baseline observation carried forward (BOCF) technique will be used for patients who do not complete the study (as will be illustrated in a corresponding trial flow diagram).

For the primary analyses at week 12, we will use analysis of covariance (ANCOVA) to compare the progressive high-load exercise group with the low-load exercise group for mean changes from baseline in the DASH score, as well as the secondary continuous outcomes. The primary model includes the change from baseline as the dependent variable, with treatment group (progressive high-load exercise or low-load exercise), corticosteroid status (yes or no), and the centre site (one, two or three) as main effects, with the baseline score as an additional covariate. The secondary analysis for the primary outcome will add the interaction term for group × corticosteroid in the primary model.

To analyse the longitudinal element of time effects of DASH in the randomised trial (repeated measures design three, six, nine, and 12 weeks), a linear approach will be used, fitted in SAS software (version 9.3 Service Pack 4; SAS Institute Inc., Cary, North Carolina, United States) using the procedure ‘PROC MIXED’ based on restricted maximum likelihood (REML) estimates of the parameters. The variable ‘patient’ will be applied as a random effects factor. Assessment of the treatment and time effects is of exploratory interest for the primary outcome in testing for a possible interaction, and both treatment and time will be used as systematic factors, using the baseline value as covariate to reduce random variation and increase power.

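### The 90% power that takes the sample to 260 is for injected versus non-injected patients within the high-load arm, not for the group × corticosteroid interaction that is the second aim and the planned test

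*Protocol article*

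**What the plan says.** The last paragraph of the Background sets the objective: "The second aim is to evaluate the possible interaction of concomitant use of corticosteroids with the exercise intervention". The section Statistical analysis plan fixes the test: "The secondary analysis for the primary outcome will add the interaction term for group × corticosteroid in the primary model".

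The section Sample size and power considerations opens its second calculation with the same objective: "As the second objective is to explore the interaction between corticosteroid use (yes or no) and exercise". It then gives a directional hypothesis about the high-load group only, and states that "a sample size of 62 patients per stratum (having progressive high-load exercise) will be required to obtain a power of at least 0.9 (90"%). The effect sought is a gap of 10 DASH points, injected against not injected, and both subgroups belong to that one exercise arm. The total of 260 follows as a consequence of this calculation, with 130 per exercise group and equal numbers injected and not injected, that is 65 in each of four cells.

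On who is injected, the section Interventions says: "Concomitant use of corticosteroid injections will be based on the orthopaedic specialist’s evaluation". It expects 25 to 50% of patients to be injected, before randomisation.

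**The concern.** The powered contrast and the planned test are different quantities. The first compares two subgroups of one exercise arm, and no low-load patient enters it. The second asks whether the injected minus non-injected difference differs between the two arms. If injection helped both arms equally, the within-arm difference could be large while the interaction is zero.

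The calculation matters because it decides the size. The primary outcome already has power 0.985 with 100 per group, so the step from 200 to 260 rests on the secondary calculation. No power is given for the interaction term. A reader could therefore take a non-significant interaction for a result with 90% power behind it.

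The powered contrast is also observational. Stratified randomisation makes the exercise arms comparable within each injection stratum; it does not make injected and non-injected patients comparable with each other. A within-arm difference mixes any injection effect with the reasons for injecting.

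**Working it through.** **Inputs.** From Sample size and power considerations: SD 17; difference 10 DASH points; 62 per stratum; total 260, 1:1 by injection, so 65 per cell; two-sided 0.05 (stated for the primary calculation, assumed to carry over). From Interventions: 25 to 50% injected. Assumed, because the documents do not give them: injection effect of 10 points with high load and 0 with low load; no dropout; any correlation between baseline and 12-week scores.

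**1. The plan's own figure.** Two-sample t-test, 62 v 62:

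- SE = 17 × √(2/62) = 3.05
- noncentrality = 10/3.05 = 3.28
- power = 0.901 (noncentral t, 122 df); with 61 per group it is 0.897

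So 62 per stratum is correct for the within-arm contrast.

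**2. The planned interaction on the same inputs.** The contrast is (injected − not injected, high load) − (injected − not injected, low load), with SE = SD × √(Σ 1/n) over the four cells.

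- Within-arm SE with 65 per stratum: 17 × √(2/65) = 2.98
- Interaction SE with 65 per cell: 17 × √(4/65) = 4.22, so twice the variance
- 10-point interaction: noncentrality 10/4.22 = 2.37, power 0.656 (256 df; 0.660 by normal approximation)

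**3. The expected injection range.** At 25% injected, the cells are 32.5 and 97.5 in each arm:

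- SE = 17 × √(2/32.5 + 2/97.5) = 4.87
- 10-point interaction: noncentrality 10/4.87 = 2.05, power 0.534
- the within-arm comparison itself falls to 0.82

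| | 50% injected | 25% injected |
|---|---|---|
| Power, 10-point interaction | 0.66 | 0.53 |
| Power, 7.5-point interaction | 0.43 | 0.34 |
| Power, 5-point interaction | 0.22 | 0.18 |
| Interaction detectable with 90% power | about 13.7 | about 15.8 |

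The 5-point row is the case where injection gains 10 points with high load and 5 with low load.

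**4. Size needed.** 90% power for a 10-point interaction, unadjusted and with equal cells, needs 122 per cell, or 488 patients; 80% needs 92 per cell, or 368.

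**5. Baseline adjustment.** The planned model includes the baseline score. With residual SD = 17 × √(1 − r²), a 10-point interaction and 65 per cell:

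| Assumed r | Power |
|---|---|
| 0.3 | 0.70 |
| 0.5 | 0.78 |
| 0.6 | 0.84 |
| 0.7 | 0.91 |

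At 25% injected, r = 0.5 gives 0.66.

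**The case against.** The strongest reply has four parts.

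First, the arithmetic is right and the contrast is openly described: the text says that the 90% is for two subgroups within the high-load arm. This stands. A reader might infer that the protocol claims 90% power for the interaction; it does not say so. The fault is that this calculation is offered in support of the interaction objective and sets the total.

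Second, one might conclude that 0.66 is the best the trial can do. The documents do not support that. The planned model adjusts for baseline, no correlation is given, and at r of about 0.7 power would reach 0.91. The low-load means are in Figure 2B, which is not available here, so a zero low-load effect is an assumption, and an opposite-direction effect would enlarge the interaction. Against this, the protocol's own calculation uses SD 17 unadjusted, the same adjustment would raise its within-arm figure too, and the 1:1 split is the favourable end of its expected range.

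Third, the objective is worded as exploratory, and the Statistical analysis plan section already promises differences with 95% confidence intervals for these analyses. Both points stand and lower the severity. They do not make a power figure for one contrast apply to another.

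Fourth, no passage says that a null interaction will be read as proof of no modification, and no within-arm test is in the analysis plan. That is true; misreading is a risk, not a stated intention.

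**Conclusion.** The concern holds as a mismatch between the powered contrast and the secondary objective, of moderate severity. It is not a calculation error: the 62 per stratum is correct for what it describes. But the figure that raises the size to 260 does not belong to the planned interaction analysis.

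The 0.66 (half injected) and 0.53 (a quarter injected) are conditional on SD 17, two-sided 0.05, no adjustment, no dropout and a 10-point interaction. They are not bounds: baseline adjustment moves them up, and an injection benefit in both arms moves them down. The non-randomised nature of the within-arm comparison is a separate matter of interpretation and does not enter these figures.

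The primary analysis is untouched: 100 per group gives 0.985, as stated, and 260 exceeds that.

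**What to change.** Keep 260 patients and the planned interaction model. In Sample size and power considerations:

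1. State that the 90% with 62 per stratum applies only to injected versus non-injected patients within the high-load arm.
2. Add the power or detectable size of the planned interaction test over the expected injection range. Unadjusted, 260 patients give 90% power for an interaction of about 13.7 points at 50% injected and about 15.8 points at 25%; for 10 points, power is about 0.66 and 0.53. State the assumed low-load injection effect and, if baseline adjustment is credited, the assumed correlation.
3. State that injected versus non-injected differences within an arm are non-randomised, and will be read neither as a steroid effect nor as the interaction test.

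The cost is wording only, with no change to recruitment, randomisation or analysis. The price is a less favourable power statement for the secondary objective.

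### The 90% power behind N = 260 assumes equal numbers injected and not injected, which is the upper limit of the protocol's own 25 to 50% forecast; over that forecast the power is 0.82 to 0.91

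*Protocol article*

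**What the plan says.** The section on sample size and power considerations first gives 100 patients per group a power of 0.985 for the primary comparison. It then turns to the second objective, the interplay of corticosteroid injection and exercise: "With an SD of 17 DASH points, a sample size of 62 patients per stratum (having progressive high-load exercise) will be required" for power of at least 0.9 "to detect a mean difference of 10 DASH points between the two subgroups within the progressive high-load exercise group". The total follows from this step: "Consequently, it is decided to include 260 patients in the study", "assuming a similar number of patients injected and not injected with corticosteroids", with 130 patients assigned to each exercise group.

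The Interventions section describes how injections come about and how common they will be: "Concomitant use of corticosteroid injections will be based on the orthopaedic specialist’s evaluation", and "Between 25 and 50% of patients are expected to receive injections". The same section and the one on randomisation and allocation concealment say that randomisation is stratified by injection status, so that injected and non-injected patients are spread evenly over the two exercise groups.

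**The concern.** The two sections use different figures for the same quantity. The sample-size section plans on half of the patients being injected; the Interventions section gives a range in which one half is the maximum. The text does not connect them.

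Stratification does not close the gap. It makes the injected share similar in the two exercise arms, but it sets no quota for either stratum. If a quarter of patients are injected, the high-load arm has about 32 injected and 98 not injected, and stratified randomisation will reproduce that imbalance in both arms.

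At stake is the figure that sets the trial's size. By the protocol's own account the primary comparison is already above 95% power with 100 per group, so the step up to 130 per group rests on the injected versus non-injected contrast. The protocol warns that power falls if 260 patients are not recruited. It gives no such warning for an injected share below one half, which its own forecast makes likely.

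**Working it through.** **Inputs (protocol article)**

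- Difference of 10 DASH points, SD 17, target power at least 0.9: Sample size and power considerations.
- Test: two-sample pooled t-test, "two-sided significance level of 0.05". This is stated for the primary comparison and is assumed to carry over; the reproduction below supports that.
- 130 patients in the high-load arm: same section.
- Injected share f from 0.25 to 0.50: Interventions.

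**Formula.** With n1 injected and n2 not injected in the arm, SE = 17 × √(1/n1 + 1/n2), noncentrality = 10/SE, and power comes from the noncentral t distribution with n1 + n2 − 2 degrees of freedom.

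**Step 1: the protocol's own figure.** For 62 v 62, SE = 17 × √(2/62) = 3.053, noncentrality = 3.275, power = 0.901. For 61 v 61, power = 0.897. The stated 62 per stratum is therefore the exact minimum for 0.90, and the arithmetic is right given equal strata.

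**Step 2: the same test over the forecast range.** n1 = 130f and n2 = 130(1 − f).

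| Injected share | n1 v n2 | SE | Noncentrality | Power |
|---|---|---|---|---|
| 25% | 32.5 v 97.5 | 3.443 | 2.904 | 0.822 |
| 30% | 39 v 91 | 3.254 | 3.073 | 0.862 |
| 37.5% (midpoint) | 48.75 v 81.25 | 3.080 | 3.247 | 0.897 |
| 50% | 65 v 65 | 2.982 | 3.353 | 0.914 |

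**Step 3: where 0.90 is reached.** 50 v 80 gives 0.899 and 51 v 79 gives 0.901. The threshold is 51/130 = 39.2%. The forecast spans 25 percentage points, and power is below 0.90 over the lower 39.2 − 25 = 14.2 of them.

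**Step 4: scale of the shortfall.** At 25% injected it is 0.90 − 0.822 = 0.078. At 44 of 130 (33.8%) power is 0.883, so from about 34% upward the shortfall is under 0.02. Holding 0.90 at 25% injected would take about 164 patients per arm, 328 in total.

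**The case against.** **The 1:1 split is declared as an assumption, and it lies inside the forecast.** True, and the arithmetic that follows from it is correct. But it lies at the limit of the range, and every other value in the range gives lower power. A reader of the sample-size section alone would not learn that.

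**The aim is secondary and described as exploratory.** This stands as a limit on the importance of the point. It does not remove it, because the total of 260 is derived from this contrast.

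**The planned analysis is an ANCOVA with the baseline score as covariate, not a t-test.** This also stands in part. The documents give no correlation between baseline and week 12. If it is assumed to be 0.3, 0.4 or 0.5, the SD shrinks by √(1 − r²) and power at 25% injected becomes 0.86, 0.88 or 0.91; at 30% it becomes 0.89, 0.91 or 0.94. The 39% threshold therefore belongs to the unadjusted test by which the protocol sized the trial. It should not be presented as a strict condition for the final analysis.

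**Stronger readings that the documents do not support**

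- A reader might infer that 90% power needs a 1:1 split, or holds only near the top of the range. It does not: as one stratum shrinks the other grows, and 51 v 79 is enough. What holds only near the top is having 62 patients in each stratum, which takes 62/130 = 47.7% injected.
- A reader might infer that drop-out erodes the margin of 65 over 62 per stratum. The statistical analysis section keeps all randomised patients, with baseline values carried forward for those who do not complete, so the numbers analysed do not fall with withdrawals.
- A reader might want power for the interaction term as well. That depends on the injection effect expected in the low-load arm, which the text does not state and which belongs to a figure not shown here.

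**Conclusion.** The inconsistency is real and moderate. The stated power of at least 0.9 holds from about 39% injected upward and is not met from 25% to about 39%. Over the protocol's own forecast the within-arm power runs from 0.82 to 0.91, and at the midpoint it is 0.897, practically on target.

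These figures assume a two-sided 0.05 level for this contrast, the same SD of 17 in both strata, an injected share in the high-load arm equal to the overall share, 130 patients in that arm, and no baseline adjustment. The primary comparison does not depend on the injected share in this way and is not affected.

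**What to change.** Reconcile the Interventions section with the sample-size section. In the latter, keep the 1:1 split as the basis of the calculation but say that it is the upper limit of the expected share, and replace the single power figure with a range. For example: with 130 patients in the high-load arm, an SD of 17 and a difference of 10 DASH points, the power of an unadjusted two-sided t-test is 0.82 if 25% are injected and 0.91 if 50% are injected; it reaches 0.90 from about 39% injected; adjustment for baseline may raise these values.

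Keep N = 260. The cost is a few lines of text and a less favourable stated figure; recruitment, randomisation and analysis do not change.

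### The fallback of 46 per group for 80% power is a complete-data, unadjusted figure: marginally short on the named t-test, with no allowance for the plan's baseline-carried-forward rule

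*Protocol article*

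**What the plan says.** The section on sample size and power in the protocol article ties recruitment to a date as well as a number: "patient recruitment stops when the total number of 260 patients has been recruited, or the deadline of Marts 2015 is reached". It accepts that power would then be lower than expected, and gives one benchmark for a 10-point difference between the arms, with SD 17: "a sample size of 46 patients per group will be required to obtain a power of at least 0.8 (80"%). That sentence names no test. The first power statement in the section does: "For a two-sample pooled t-test of a normal mean difference with a two-sided significance level of 0.05". The SD comes from "we expect a mean baseline of 40 points on the DASH questionnaire with an SD of 17". The 10-point contrast comes from two expected changes. For the intervention arm the section writes "We expect a 50% change (change from 40 to 20 DASH points) in the progressive high-load exercise group". For the control arm it expects half of that improvement: "25% (change from 40 to 30 DASH points) in the low-load exercise group".

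The section on statistical analysis then sets the primary analysis. All randomised patients are included, the outcome is change in DASH at week 12, and the model is an ANCOVA with treatment, corticosteroid status, centre and baseline score. For missing data, "a baseline observation carried forward (BOCF) technique will be used for patients who do not complete the study". The sample-size section gives neither a dropout rate nor a correlation between baseline and week-12 scores.

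**The concern.** The fallback power and the missing-data rule do not describe the same analysis. The power figure treats each randomised patient as a completer who shows the full expected change. The analysis rule gives each non-completer a change of zero and keeps that patient in the denominator. Because the two arms are expected to improve by different amounts (20 and 10 points), zeros in equal proportion pull the arm means together. This happens with equal dropout in both arms, so it is separate from any bias due to unequal dropout.

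The stake is limited but concrete. If the trial closed early with about 46 per group, a reader could take 80% power from this sentence when the protocol has not shown it for the analysis it prescribes.

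**Working it through.** **Inputs.** From the sample-size section: difference 10, SD 17, two-sided 0.05, expected changes 20 and 10. From the analysis section: baseline carried forward for non-completers, and adjustment for baseline. Assumed, because the document does not state them: dropout d, equal in both arms, at 5%, 10% and 20%; baseline to week-12 correlation r at 0, 0.3, 0.5 and 0.7.

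**1. The printed figures.** Normal approximation: n = 2(1.960 + 0.842)² × 17²/10² = 45.4, rounded up to 46, with power 0.805. The printed 46 is therefore reproduced.

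Pooled t-test, noncentrality 10/(17√(2/n)):
- n = 46: 2.82 on 90 df, power 0.797
- n = 47: 2.85 on 92 df, power 0.806

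The neighbouring figures follow the t-test. 100 per group gives 0.985, as printed. For at least 0.9, 61 gives 0.897 and 62 gives 0.901, and 62 is printed (the normal approximation would need only 61). So 46 meets its threshold by the approximation but not by the test that fits the other two figures.

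**2. Effect of carrying the baseline forward, unadjusted.** The expected difference is 10(1 − d). With m the expected change in an arm (20 or 10), the mean of m² is (400 + 100)/2 = 250. The average variance is then:
- SD 17 as the week-12 score SD: 289 + d(1 − d) × 250
- SD 17 as the SD of change: 289(1 − d) + d(1 − d) × 250

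At d = 10% the difference is 9. The score reading gives variance 289 + 22.5 = 311.5 (SD 17.65). The change reading gives 260.1 + 22.5 = 282.6 (SD 16.81). Power of the t-test at 46 per group:

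| Dropout (assumed) | SD 17 = week-12 score | SD 17 = change |
|---|---|---|
| 0% | 0.797 | 0.797 |
| 5% | 0.738 | 0.759 |
| 10% | 0.677 | 0.719 |
| 20% | 0.553 | 0.635 |

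Simulation of the same t-tests agreed to within 0.01.

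**3. Baseline-adjusted ANCOVA, simulated.** 46 per group, score SD 17 at both times, non-completers set to baseline, 8,000 trials per cell. The model has treatment and baseline only; corticosteroid status and centre were left out.

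| Correlation r (assumed) | 0% dropout | 10% | 20% |
|---|---|---|---|
| 0 | 0.80 | 0.67 | 0.56 |
| 0.3 | 0.82 | 0.73 | 0.63 |
| 0.5 | 0.89 | 0.81 | 0.72 |
| 0.7 | 0.97 | 0.92 | 0.85 |

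Repeat simulations of the 10% column differed by about 0.01 (for example 0.93 at r = 0.7).

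**4. The planned size.** At 130 per group, unadjusted power is 0.984 (score reading) or 0.990 (change reading) at 10% dropout, and 0.943 or 0.974 at 20%.

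**The case against.** The strongest reply is that the primary analysis is not a t-test. It adjusts for baseline, and that recovers power. With complete data, 46 per group gives about 0.82 at r = 0.3 and 0.89 at r = 0.5. At 10% dropout it still reaches 0.81 at r = 0.5 and 0.92 at r = 0.7. If 17 were the SD of both the score and the change, r would be 0.5, since the SD of change is 17√(2(1 − r)). This reply stands: the unadjusted values are not the power of the written analysis. It does not rescue the sentence as printed, because the protocol states no correlation and takes no credit for adjustment, and at lower correlations 80% is not reached.

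Second, 0.797 rounds to 0.80, the fallback sentence names no test, and 46 is exactly what the normal approximation gives. That also stands. A reader might infer a calculation error; the document does not support that. The slip is one patient per group, and is noticeable only because the neighbouring figures follow the exact test and the wording promises at least 0.8.

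Third, the figure illustrates a contingency. Nothing says that the trial would stop at 46 per group or that 46 would suffice. The section already warns of reduced power, and its 0.985 at 100 per group also informs a shortfall from 130. This is fair, and it limits how much weight the point can carry.

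**Conclusion.** The point holds as a minor restatement. The fallback is a complete-data, unadjusted figure, 0.3 percentage points short of its threshold on the named test, with no allowance for the missing-data rule that the same article prescribes. For the planned ANCOVA at an assumed 10% dropout, power at 46 per group lies between about 0.67 and 0.93 for correlations from 0 to 0.7, so 80% is neither assured nor excluded.

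Two stronger readings should be resisted.
- A reader might infer that the planned analysis has 68% power at 46 per group, or that 54, 62 and 82 per group are needed at 5%, 10% and 20% dropout. Those sizes belong to an unadjusted comparison with 17 as the score SD. On the change reading they are 51, 56 and 68, and neither set applies to the baseline-adjusted model.
- A reader might infer that the trial is underpowered. At the planned 130 per group, unadjusted power stays at about 0.94 or higher up to 20% dropout.

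The score reading of SD 17 is the more natural one, since the SD is drawn from baseline scores and applied to week-12 means of 20 and 30. The article does not settle it, because its primary outcome is change.

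**What to change.** In the fallback sentence, replace 46 with 47 per group and label it as the complete-data, unadjusted t-test figure. State whether SD 17 refers to the week-12 score or to the change. Add the power at that size for the planned ANCOVA with baseline carried forward, at a stated dropout rate and baseline to week-12 correlation, or over a range of both. If recruitment closes at the deadline, quote that power and not the bare 80%. The 260 target need not change. The cost is a few lines of text and a short simulation, with no extra patients or data.
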